### Early phase outcome data

Patient outcome and follow-up data related to initial findings and hospital stay will be obtained from the hospital by the trial research nurse at a time beyond 30 days from the injury and include: (1) Injury Severity Score (ISS) and Abbreviated Injury Scores (AIS) for each body region [27,28]; (2) injuries identified on independent review of first cerebral imaging by computerised tomography (CT) or magnetic resonance imaging (MRI); (3) 24 hour and 30 day mortality; (4) survival to hospital discharge; and, (5) length of intensive care unit (ICU) stay including number of ventilator days.

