#### Statistical analysis for aim 2: associations of nirs tissue oximetry with acute phase outcomes

The area under the curve for cerebral oximetry value ≤ 45% (minutes x desaturation points ≤ 45%) will be used as an independent variable for statistical analyses as described previously [34]. Patients with one or more episodes of cerebral oximetry value ≤ 45% for 1 minute will be classified as experiencing a decline in cerebral oxygen saturation.

We will define 3 NIRS cerebral oximetry patient groups:NIRS 1 (cerebral oximetry values remain > 45% i.e. area under the curve = 0 min%).NIRS 2 (cerebral oximetry values ≤ 45% for > 0 min up to the median area under the curve for cerebral oximetry value ≤ 45% to be determined).NIRS 3 (cerebral oximetry values ≤ 45% for more than the median area under the curve for cerebral oximetry value ≤ 45% to be determined).

The total duration (minutes) of StO_2_ ≤ 45%, longest duration (minutes)

StO_2_ ≤ 45%, minimum and average StO_2_ will be derived for each patient. These variables will be compared between NIRS 1, NIRS 2 and NIRS 3 groups using Kruskal-Wallis analysis of variance to check the validity of this grouping.

A chi-square test will be used to assess the association between cerebral oximetry values by comparing patients in each of the above groups in their association with the following injury patterns on cerebral imaging: no intracranial pathology, intracerebral lesions present, subdural haematoma, extradural haematoma, traumatic subarachnoid haemorrhage and diffuse injury. The same analysis will also be repeated to establish associations with 24 hour and 30-day mortality and survival to discharge.

In the multivariate analysis, an ordinal logistic regression under a proportional odds model with NIRS 1 as the reference group will be used with the six types of injury on cerebral imaging listed above included as an independent variable after adjusting for ISS, age, sex and other covariates (mean arterial pressure, first recorded GCS, peripheral oximetry, end-tidal CO_2_, HbT) in a stepwise fashion. A score test will be used to verify the proportional odds assumption in the final model. The unadjusted and adjusted odds ratios and 95% confidence intervals will be reported. Significance will be set at P < 0.05.

### Outcomes for aim 2

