#### Statistical analysis for aim 3: associations with long-term outcomes

Utilising the same groupings for NIRS tissue oximetry (NIRS 1 through 3), associations with EGOS (grouped into EGOS < 2, 2–4 and 5–8), GOS and CANS will be tested with the same multivariate analyses and ordinal logistic regression approach described above. This will include adjustment for ISS, age, sex and other covariates. For validation of the model for Aims 2 and 3, we will internally validate the models using bootstrapping methods on 1000 samples. All data analysis will be performed using SPSS version 21 and STATA 13.1 software (StataCorp, College Station, TX).

### Outcomes for aim 3

This analysis will establish simple associations between NIRS cerebral oximetry values and the subsequent long-term functional recovery of patients with TBI. This would potentially allow early identification of patients with more severe injuries to optimise early intervention and engagement of rehabilitation services.

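### Early mortality and survival to discharge are tested against NIRS group only by an unadjusted chi-square, which cannot show that NIRS carries information about early death beyond injury severity

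*Protocol article*

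**What the plan says.** All references are to the protocol article.

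- **Aim 2 statistical analysis, univariate part.** Patients are split into NIRS 1, 2 and 3 by the area under the 45% threshold. The stated test is: "A chi-square test will be used to assess the association between cerebral oximetry values by comparing patients in each of the above groups", applied to the imaging injury patterns. The next sentence is: "The same analysis will also be repeated to establish associations with 24 hour and 30-day mortality and survival to discharge".
- **Aim 2, multivariate part.** This follows in a separate paragraph. It describes an ordinal logistic model of NIRS group "with the six types of injury on cerebral imaging listed above included as an independent variable after adjusting for ISS, age, sex and other covariates". The other covariates are "mean arterial pressure, first recorded GCS, peripheral oximetry, end-tidal CO_2_, HbT". Death and survival to discharge do not appear in it.
- **Aim 3 statistical analysis.** The adjusted approach is carried over as follows: "associations with EGOS (grouped into EGOS < 2, 2–4 and 5–8), GOS and CANS will be tested with the same multivariate analyses". The three early survival outcomes are again not named.
- **Early phase outcome data.** The outcomes "24 hour and 30 day mortality; (4) survival to hospital discharge" are collected, and so are "Injury Severity Score (ISS) and Abbreviated Injury Scores (AIS) for each body region".
- **Novel analysis methods applied to acute phase outcomes.** The Aim 1 signal-analysis results are also compared with 24-hour and 30-day mortality. That comparison is not by NIRS group, and no adjustment is stated.

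**The concern.** For these three outcomes the article names a method, and it has no covariates. For the neighbouring outcomes it names models adjusted for ISS, age, sex and first GCS. The gap is therefore an uneven choice of method rather than detail left to an analysis plan.

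The cohort is observational and mixed: the Power analysis section expects 1210 recruits to yield 242 with severe TBI, which is 242/1210 = 20%. More severely injured patients are plausibly more likely both to desaturate and to die. A significant chi-square would then appear even if NIRS added nothing to what GCS and ISS already show. The Discussion wants the study to support later work in which treatment is guided by oximetry. For that purpose, information beyond severity is what counts.

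**Working it through.** **1. The plan's own figure.** By Fisher's z for r = 0.22, two-sided 0.05 and 90% power: n = ((1.960 + 1.282)/atanh(0.22))² + 3 = 213.06. Adding the 29 failed monitoring attempts gives 213 + 29 = 242, as stated. The sample size is not in dispute. It supplies the two cohort sizes used here: 213 evaluable severe TBI patients, and 1210 × 0.88 ≈ 1065 evaluable patients overall.

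**2. A case that can be checked by hand (assumed inputs).** Take 213 severe TBI patients in two equal halves. In the worse half 60% desaturate and 45% die; in the other half 30% desaturate and 15% die. Within each half, NIRS has no relation to death. Desaturating patients are split evenly between NIRS 2 and NIRS 3.

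- Death if desaturated: (0.60 × 0.45 + 0.30 × 0.15)/(0.60 + 0.30) = 0.315/0.90 = 35.0%.
- Death if not: (0.40 × 0.45 + 0.70 × 0.15)/(0.40 + 0.70) = 0.285/1.10 = 25.9%.
- Crude odds ratio: (0.350/0.650)/(0.259/0.741) = 1.54.
- Noncentrality: 213 × [0.55 × (0.259 − 0.300)² + 0.45 × (0.350 − 0.300)²]/(0.30 × 0.70) ≈ 2.1. On 2 df at the 0.05 level this gives a rejection rate of about 23% (24% in simulation).

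With weaker links between severity and desaturation (60% v 40%, then 50% v 40%) the crude rejection rate falls to about 13% and 7%.

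The same model for the whole cohort has 20% severe and deaths of 30% v 2%. Desaturation of 30% v 20% gives 20-26% rejection (odds ratio 1.4); 60% v 20% gives about 99% (odds ratio 3.0).

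**3. A continuous-severity model (assumed inputs).** Severity is standard normal. NIRS exposure has correlation r with it and is cut into groups of 50/25/25%. Death depends on severity only, with an odds ratio of 2 or 3 per SD. Rejection rates of the 3 × 2 chi-square at 0.05, for odds ratio 2 to odds ratio 3:

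| Evaluable patients | Deaths | r = 0.22 | r = 0.4 |
|---|---|---|---|
| 213 | 30% | 10-17% | 26-49% |
| 213 | 10% | about 8-11% | – |
| 1065 | 10% | 18-39% | 53-87% |
| 1065 | 5% | about 12-24% | – |

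Repeat runs differ by a point or two: with 1,000 replicates the simulation standard error at 9% is √(0.09 × 0.91/1000) ≈ 0.9 points. Rounded across runs, r = 0.22 gives about 9-17% at 213 patients and about 13-40% at 1065. With 213 patients and 30% deaths at r = 0.22, the NIRS 3 versus NIRS 1 odds ratio produced by severity alone is 1.35 to 1.50.

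**4. What adjustment achieves.** If the logistic model contains the exact severity variable that drives death, the NIRS test rejects in about 4-6% of studies. Real covariates measure severity imperfectly. If they capture half of its variance (assumed), the adjusted test rejects in about 5-14% of studies at r = 0.22 and 6-33% at r = 0.4. Adjustment reduces the confounding but does not abolish it.

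**The case against.** The strongest reply is that the plan promises associations, not causes or independence from severity. Aim 3 even lists early identification of severely injured patients as a use, and for that a marker of severity is welcome. If NIRS tracks severity and severity drives death, a crude association exists and the chi-square is right to find it. This stands: a reader might infer that the test's 5% error rate is broken, but it holds for the null hypothesis being tested. The rates above show how often the result would be misread as information beyond severity.

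Other points also stand in part:

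- A reader might infer that death never receives an adjusted analysis. It does, through the lowest EGOS group (< 2) in the Aim 3 model at 6 and 12 months, but not at the three early time points.
- Subgroup analyses in severe TBI and ISS > 15 narrow the severity range. The 213-patient figures show that confounding can remain within such a group.
- The summary of Aim 2 outcomes speaks of types of brain injury and does not mention mortality, so little of the study's headline rests on these tests.
- The article condenses a fuller plan. That would excuse silence on method, but here a method is stated.

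Two inputs must not be over-read. The 0.22 is the correlation with admission GCS that the study is powered to detect, not a value the plan presumes; it says prior datasets are lacking. The 30% deceased is an EGOS-group share given in a six-month context, not 24-hour or 30-day mortality, which is why lower death rates are shown too.

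**Conclusion.** The point holds as a limit on interpretation. For 24-hour mortality, 30-day mortality and survival to discharge, the only stated NIRS-group analysis is an unadjusted chi-square, a weaker method than the plan gives imaging findings, EGOS, GOS and CANS. It can support a statement of crude association and no more.

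The size depends on inputs the documents do not give: the NIRS-severity correlation, the effect of severity on death, the group shares and the early death rates. At a correlation of 0.22, severity alone makes the test significant in about 9-17% of studies of 213 patients and about 13-40% of studies of 1065; the larger figures in the table need stronger assumed links. It would go too far to say that the study is invalid, or that adjustment restores a clean 5% level. This is a cheap and worthwhile improvement, not a fatal fault.

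**What to change.** In the Aim 2 statistical analysis section:

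1. Keep the chi-square and label it the crude result.
2. For each of the three outcomes, add a logistic regression on NIRS group (NIRS 1 as reference), adjusted for prespecified first recorded GCS, age and sex, with ISS added as in the plan's other models. Use a penalised fit or fewer covariates if deaths are few.
3. Report crude and adjusted odds ratios with 95% confidence intervals side by side, and show the adjusted results with and without ISS.
4. Base any statement that NIRS is associated with early death independently of severity on the adjusted result, and say that residual confounding may remain.

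The cost is a few sentences and a small set of extra models on data already planned for collection. There are three drawbacks. Intervals will be wider. Few 24-hour deaths may limit the number of covariates. ISS includes the head injury that NIRS is meant to reflect, so adjusting for it may remove some of the signal of interest; that is the reason for showing both versions.

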### Study plan

The *hypothesis* is that NIRS tissue oximetry can provide direct real-time cerebral physiological data that provides an insight into rapidly developing brain pathology in TBI and its management, as well as early associations with long-term outcomes. Three aims will be delivered to achieve this:To establish methods of analysing the NIRS tissue oximetry monitoring parameter time series that correspond with evolving pathology in the TBI.To establish the association between NIRS tissue oximetry monitoring parameters and acute pathology in patients with TBI.To establish the association between NIRS tissue oximetry monitoring parameters and the long-term recovery of patients after TBI, as assessed at follow-up to 12 months.

This research will therefore be conducted in a prehospital setting, providing early monitoring data in patients likely to have TBI with a plan for subsequent follow-up data collection to examine both acute and long-term outcomes. Novel analysis methods as featured in Aim 1 will provide better options for demonstrating the associations described in aims 2 and 3.

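### The Aim 2 regression names no dependent variable and makes no provision for patients with several lesions, so the meaning and direction of its adjusted odds ratios are undetermined

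*Protocol article*

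**What the plan says.** All of the following is in the protocol article.

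- **Study plan.** Aim 2 is worded "To establish the association between NIRS tissue oximetry monitoring parameters and acute pathology in patients with TBI". It asks for an association and fixes no direction.
- **Statistical analysis for aim 2, exposure.** The area under the curve for cerebral values at or below 45% "will be used as an independent variable for statistical analyses as described previously". It is then cut into three groups ("We will define 3 NIRS cerebral oximetry patient groups"): none, up to the median, and above the median.
- **Same section, adjusted model.** The text says "an ordinal logistic regression under a proportional odds model with NIRS 1 as the reference group will be used". Injury type is then placed among the predictors of that same model, in these words: "with the six types of injury on cerebral imaging listed above included as an independent variable". The model also takes in ISS, age, sex and five further covariates, stepwise. No dependent variable is named.
- **Same section, injury categories.** These are "no intracranial pathology, intracerebral lesions present, subdural haematoma, extradural haematoma, traumatic subarachnoid haemorrhage and diffuse injury". No rule is given for a patient with two or more of the five lesion types.
- **Statistical analysis for aim 3.** Associations with grouped EGOS, GOS and CANS "will be tested with the same multivariate analyses and ordinal logistic regression approach described above".

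**The concern.** A regression needs one variable on the left-hand side. Here the NIRS exposure and the injury type are each called independent, and the covariates are predictors too, so the outcome has to be guessed. The guess matters because proportional odds requires an ordered outcome. The NIRS groups have an order and the injury types do not. The type of model, the quantity estimated and its direction all depend on which guess is made.

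The wording also treats six types, one of them being no pathology, as a variable in the singular. If that means one exclusive factor, each patient needs a single label, and the text gives no way to choose it.

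This is the only adjusted model described for Aim 2, and Aim 3 borrows it. If it stays open, the outcome, the direction and any ranking of lesions could be settled after the data are seen.

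**Working it through.** The plan gives no figure on this point, so the check sets the readings side by side and illustrates each by simulation. **Prevalences, effects and group shares below are assumptions, not document figures.**

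**Assumed inputs for readings 1 to 3.** Five independent lesion indicators with prevalences 35, 30, 12, 35 and 25%. Log odds ratios 0.7, 0.7, 0, 0.3 and 0.7, so true odds ratios are 2.01, 2.01, 1.00, 1.35 and 2.01. NIRS group is generated from a proportional odds model. Among simulated patients with any lesion, 52% had more than one. N = 60,000 for readings 1 and 2, and 6,000 for reading 3.

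**Reading 1: NIRS group is the ordinal outcome, with separate lesion indicators as predictors.** Estimated odds ratios were 2.00, 1.96, 1.01, 1.31 and 2.02, so the assumed values are recovered. The model is sound, but it departs from the text in three ways:
- It makes the NIRS exposure dependent, although the section calls it independent.
- A cumulative-logit outcome has no reference group; that phrase fits a categorical predictor.
- It cannot move unchanged to Aim 3, where EGOS is the ordered outcome.

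**Reading 2: as reading 1, but injury is one exclusive six-level factor.** Each patient takes the label of the highest-ranked lesion present.

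| Lesion | True OR | Ranked first to fifth | Ranked fifth to first |
|---|---|---|---|
| First | 2.01 | 3.22 | 1.93 |
| Third | 1.00 | 1.39 | 1.61 |
| Fifth | 2.01 | 2.02 | 3.46 |

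The cause is that a top-ranked label also carries the effects of the other lesions those patients have. For the first lesion ranked top, the approximate log odds ratio is 0.7 + 0.30×0.7 + 0.12×0 + 0.35×0.3 + 0.25×0.7 = 1.19, and exp(1.19) = 3.29, close to the simulated 3.22. For the third lesion under the reverse ranking it is 0 + 0.35×0.7 + 0.30×0.7 = 0.455, and exp(0.455) = 1.58, close to 1.61. A lesion with no effect therefore appears to have one.

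**Reading 3: injury type is the outcome of the proportional odds model.** The NIRS 3 versus NIRS 1 odds ratio ran from 0.44 to 2.37 over 25 random orders of the six categories. With no pathology fixed as lowest, it ran from 1.21 to 2.49 over the orders sampled. The data were the same throughout; only the arbitrary order changed. Proportional odds is not valid for this outcome.

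**Unadjusted chi-square.** The Power analysis allows for 29 failed recordings among 242 subjects, so n = 242 − 29 = 213. Null simulations used 213 patients and an assumed 60/20/20% NIRS split. If multi-lesion patients are counted in several columns of one 3 × 6 table, the test at nominal 5% rejected in 0.4 to 0.8% of runs with prevalences of 15 to 45%, and in 0.9 to 2.0% with prevalences of 12 to 35%. Separate 3 × 2 tests rejected in about 4 to 6%, as intended.

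**The case against.** The strongest reply is that one workable reading exists. The section defines three ordered NIRS groups, names a proportional odds model and puts injury type among the predictors, so NIRS group can be taken as the outcome. Predictors need no order, Aim 2 asks only for an association, and imaging done after monitoring does not invalidate an associational odds ratio. All of this stands. A reader might infer that the model cannot answer Aim 2 at all; the documents do not support that.

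Three further limits also stand:
- **Coding.** Reading the six types as one exclusive factor rests on a singular article. Separate indicators are not excluded, and a condensed article may leave coding to an analysis plan. That lesions coexist is plausible but is not stated.
- **Aim 3.** A reader might infer that six-month EGOS is meant to predict the prehospital NIRS group. The Aim 3 heading, the stated use for early identification of severe injury, and the trend test across EGOS groups in the Power analysis all make EGOS the natural outcome.
- **Chi-square.** The protocol does not specify a pooled 3 × 6 table. Its wording fits one comparison per injury pattern equally well, and then the error rate is correct.

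The reply does not remove the contradiction. The workable reading for Aim 2 reverses the role that the same section gives to NIRS exposure, and it runs opposite to the natural reading of Aim 3, which is said to use the same approach. That is a conflict between printed statements, not detail left for another document.

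**Conclusion.** The point holds as a specification defect. NIRS exposure and injury type are both labelled independent, no dependent variable is named, and several lesions in one patient are not provided for, so the adjusted odds ratios are undetermined in meaning and direction.

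The consequence depends on the reading. With injury type as ordinal outcome, the result is uninterpretable. With NIRS group as outcome and lesion indicators, the estimate is valid but contradicts the stated role of the exposure and does not carry over to Aim 3. With one exclusive factor and coexisting lesions, the odds ratios depend on an arbitrary ranking. The sizes shown rest on assumed prevalences, effects and independence of lesions; they illustrate the problem and do not predict this study's results.

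The chi-square error rate is wrong (about 0.4 to 2% against 5%) only for a pooled table with multiple counting. The error would then be towards missing real associations, not towards false positives.

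**What to change.** Reconcile the Aim 2 and Aim 3 analysis sections before the data are analysed:

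1. State that NIRS group, with NIRS 1 as reference, is the predictor in both aims.
2. For Aim 2, analyse each of the five lesion types as present or absent, and any intracranial pathology likewise. Use a 3 × 2 chi-square unadjusted and binary logistic regression adjusted. A patient with several lesions then contributes to each relevant analysis.
3. For Aim 3, name EGOS (grouped as planned), GOS and CANS as the dependent variables of the proportional odds models.

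A valid alternative for Aim 2 is to keep NIRS group as the ordinal outcome with a separate indicator for each lesion. The text should then say so, withdraw the label of independent variable for NIRS exposure in that model, and state that Aim 3 runs the other way.

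The cost is a change of wording and a few more models, with no new data. Rare lesions will have wide intervals.

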## Background

Traumatic brain injury (TBI) is a significant cause of death and severe disability [1]. Estimates suggest that long term costs of caring for people with moderate and severe TBI add $8.6 billion to health spending per year in Australia [2]. Despite advances in hospital care of patients with TBI, minimal improvements in outcome have been evident over the last twenty years [1].

In the setting of TBI, it is not only the initial injury that is responsible for patient outcome. After the initial insult, the brain is susceptible to further damage if normal physiologic conditions are not restored. Such insults include low blood pressure or hypoxia [3,4]. The primacy of hypoxia and hypotension in the debate has guided the development of consensus guidelines for prehospital management of patients with TBI with an emphasis on regular blood pressure measurements and checking oxygen saturations [5]. However, having this knowledge to guide monitoring care has not resulted in significant changes to patient outcomes.

Peripheral measurements such as non-invasive blood pressure and pulse oximetry remain relatively crude measurements distant to the tissue of most interest; the brain itself. Additional monitoring options that have become available in the hospital such as jugular venous bulb oximetry, direct tissue oximetry and intracranial pressure measurement are not appropriate to the prehospital environment [6-8]. In the New South Wales metropolitan setting, the time spent in the prehospital treatment phase before reaching a trauma centre averages over one hour [9]. This represents a significant period of vulnerable time where monitoring information relevant directly to cerebral tissue is absent.

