### NIRS monitoring data

Each NIRS oximetry probe will continually produce 4 streams of data: StO_2_; HbT; HbO_2_; and HbD with values recorded every 4 seconds. Standard clinical monitoring will be recorded at the same time as the NIRS oximetry data captured by the EQUANOX device. This will include peripheral pulse oximetry, end-tidal capnography (where indicated for patient care), heart rate and non-invasive blood pressure and will be updated on the record every ten seconds. This general observations data will be time-matched to the NIRS oximetry monitoring data to allow direct comparisons of values in data analysis, particularly in the signals analysis related to Aim 1. Clinically relevant information such as any degree of prehospital hypoxia or hypotension will therefore be time-matched to the NIRS oximetry monitoring data.

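### Aims 2 and 3: NIRS exposure is a depth-by-time burden, but blood pressure and SpO2 have no matching form and can drop out by stepwise selection, so adjusted NIRS odds ratios may retain confounding by transient systemic insults

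*Protocol article*

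**What the plan says.** The statistical analysis section for Aim 2 gives the NIRS variable a full derivation: "The area under the curve for cerebral oximetry value ≤ 45% (minutes x desaturation points ≤ 45%) will be used as an independent variable". Three patient groups follow. NIRS 1 has zero area, NIRS 2 a positive area up to the median, and NIRS 3 is described as "cerebral oximetry values ≤ 45% for more than the median area under the curve for cerebral oximetry value ≤ 45% to be determined". Total and longest duration at or below 45%, and minimum and average StO2, are also derived for each patient.

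The adjustment set for the ordinal model is ISS, age, sex and "other covariates (mean arterial pressure, first recorded GCS, peripheral oximetry", followed by end-tidal CO2 and HbT, with the adjustment made stepwise. GCS carries a time point (first recorded). Mean arterial pressure and peripheral oximetry carry no summary, cut-off or window.

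The Aim 3 section uses the same NIRS groups and regression approach: "This will include adjustment for ISS, age, sex and other covariates".

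Two other sections bear on this. The Background names low blood pressure and hypoxia as insults that damage the brain further after the initial injury, and says of the existing monitors: "Peripheral measurements such as non-invasive blood pressure and pulse oximetry remain relatively crude measurements distant to the tissue of most interest". The section on NIRS monitoring data has NIRS values every 4 seconds and general observations updated every ten seconds, and says that "any degree of prehospital hypoxia or hypotension will therefore be time-matched to the NIRS oximetry monitoring data". It directs this matching particularly to Aim 1. Neither the Aim 2 nor the Aim 3 analysis text draws on it.

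**The concern.** Systemic hypotension and hypoxia can plausibly lower cerebral StO2, and the protocol itself says that they worsen brain damage. They are therefore candidate common causes of the NIRS grouping and of poor outcome. Adjustment removes that shared component only as far as the covariate measures it.

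The two sides of the adjusted model are not specified alike. The NIRS burden accumulates every dip at or below 45%, while the form of the systemic covariates is open. A first value can precede an episode, and a mean dilutes it. Stepwise selection adds a second route: a noisy summary of blood pressure or SpO2 may fail the selection criterion and leave the model, so that its share of the outcome association passes to whatever remains.

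At stake is the reading of the adjusted odds ratios. If cerebral oximetry is to offer something beyond the monitors already in use, these are the estimates that a reader will look to. The concern is greatest for functional outcome in Aim 3, where the protocol's own account links systemic insults to the result.

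**Working it through.** **The plan's own figure.** The Power analysis section gives 242 patients with severe TBI for a correlation of 0.22, 90% power and two-sided 0.05, including 29 failed recordings. By Fisher's z, n = ((1.960 + 1.282) / atanh(0.22))² + 3 = 213.06. The evaluable number is 242 − 29 = 213, with power 0.8999. The figure reproduces. It does not bear on this point, except that it supplies n = 213.

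**Why the form of the covariate matters.** One minute at or below 45% is enough for a patient to be classed as having a decline in cerebral saturation. At the stated rates that minute holds 60/4 = 15 NIRS values and 60/10 = 6 systemic record entries. If a recording lasts 30 to 60 minutes (an assumption; the Background puts the average prehospital phase above one hour), a one-minute systemic episode carries a weight of only 1/30 to 1/60 (3.3% to 1.7%) in a mean. A minimum, or a time or area below a cut-off, would keep it.

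**Illustrative simulation.** The documents give no figure for the confounding, so every input below except n and the test level is an assumption.

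- Systemic burden B is standard normal.
- NIRS burden = a·B + √(1 − a²)·noise, with a = 0.3, 0.5 or 0.7. Half of patients have zero area; the rest are split at their median.
- Systemic summary M = ρ·B + √(1 − ρ²)·noise, with ρ from 0.3 to 0.95.
- Binary outcome with log-odds 0.8·B and no NIRS effect given B.
- n = 213; logistic model with one systemic covariate plus NIRS group; 2-df likelihood-ratio test of NIRS group at 0.05; 600 runs per cell.

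Each cell shows the rejection rate, with the median odds ratio for NIRS 3 against NIRS 1 in brackets. The true odds ratio given B is 1.

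| a | adjusted for B itself | ρ = 0.95 | ρ = 0.8 | ρ = 0.6 | ρ = 0.3 |
|---|---|---|---|---|---|
| 0.3 | 4.5% (0.96) | 4.7% (1.06) | 8.0% (1.22) | 11.0% (1.35) | 20.8% (1.51) |
| 0.5 | 5.5% (1.00) | 3.8% (1.09) | 12.2% (1.40) | 24.5% (1.63) | 46.5% (2.04) |
| 0.7 | 3.3% (0.99) | 6.3% (1.20) | 19.7% (1.71) | 54.7% (2.29) | 76.7% (2.85) |

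The Monte Carlo standard error at 5% is √(0.05 × 0.95 / 600) = 0.9 percentage points, so the first two result columns are compatible with a nominal test. The error then rises as the summary tracks the burden less well. Removal of the covariate by selection corresponds to ρ = 0, which was not run and lies beyond the last column.

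**What the simulation is not.** It has one covariate, a binary outcome and NIRS as predictor. The Aim 2 ordinal model reads differently: NIRS 1 is the reference group and injury type enters "with the six types of injury on cerebral imaging listed above included as an independent variable", which makes NIRS group the outcome. That conflicts with the earlier statement that the NIRS area is an independent variable. The simulation shows the mechanism and does not estimate this study's error rate.

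**The case against.** The strongest case against is that the document never says how mean arterial pressure and SpO2 are summarised. A reader might infer that they enter only as plain first or mean values, and that the plan therefore credits NIRS with an independent effect. Neither inference is supported. The form is unstated, a minimum or a time below a cut-off would fit the text equally well, and a journal article may leave such derivations to a fuller document. The plan speaks of associations, and simple ones for Aim 3, rather than of an independent effect. It also already reports unadjusted and adjusted odds ratios.

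Further objections have weight:

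- The Background says that systemic insults add damage after the injury. It does not say that they produce subdural, extradural or subarachnoid bleeding on first imaging, so the confounding path is weak for the Aim 2 imaging comparison.
- Hypotension or hypoxia may harm the brain through cerebral desaturation, in which case part of what adjustment removes is mediation rather than bias.
- The simulated sizes rest on outside assumptions and omit ISS, age, GCS and the other listed covariates.
- Non-invasive pressure is intermittent; a record refreshed every ten seconds does not create new cuff readings.

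All of this limits the point without removing it. The stepwise rule is stated in the document, so possible loss of the systemic covariates is a feature of the plan as written and not a missing detail. The time-matched record that would support a better covariate is already collected. The existing contrast of unadjusted with adjusted odds ratios changes all covariates together, so it does not isolate the systemic signals.

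**Conclusion.** The point holds in a limited form. NIRS is defined as a burden over the recording; mean arterial pressure and SpO2 have no burden or episode form and are exposed to stepwise removal. Adjusted NIRS odds ratios may therefore retain confounding by transient hypotension or hypoxia, chiefly for functional outcome in Aim 3, and only weakly for injury type on first imaging.

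The size cannot be determined from the documents. Under the assumptions shown, with n = 213 and no true NIRS effect, false positives run from near nominal (3.8–6.3%) at a correlation of 0.95 between systemic summary and burden to 11–55% at 0.6. Where this study would fall depends on a summary that the protocol does not name. It would go too far to say that systemic insults will be reported as a cerebral effect: a well-chosen summary kept in the model would largely prevent it. This is a worthwhile, low-cost improvement and not a flaw that invalidates the analysis.

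**What to change.** 1. First reconcile the Aim 2 ordinal model: state whether NIRS group or injury type is the outcome, and make the description of the NIRS area as an independent variable agree. State the direction for Aim 3 as well.
2. In both analysis sections, derive a MAP and an SpO2 summary for each patient from the time-matched record over the same window as NIRS: the minimum, or time or area below a cut-off fixed in advance. The cut-off serves analysis only.
3. Keep both summaries in every adjusted model, outside the stepwise selection.
4. Report the NIRS association with and without these two terms, all other covariates unchanged, and say that part of any difference may be mediation.

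The cost is a few lines of analysis text and a derivation step, with no new data collection. The downsides are that the MAP burden will be approximate because cuff readings are intermittent (SpO2 is less affected), and that the adjusted NIRS association may shrink.
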